## Abstract

Medications for opioid use disorder (MOUD) are effective in reducing opioid use, but retention to buprenorphine remains suboptimal among OUD patients. Integration of computer-based cognitive behavioral therapy (CBT4CBT) and utilization of recovery coaches (RCs), called RC + CBT4CBT-Buprenorphine, into OUD care could improve drug use and retention in care among patients taking buprenorphine. The OVERCOME II (**O**UD Inter**ve**ntion **R**ecovery **C**oach CBT and **O**UD **Me**dications II) study is a three-arm 1:1:1 randomized clinical trial designed to test the remotely delivered RC + CBT4CBT-Buprenorphineintervention as an adjunct to buprenorphine treatment for patients with OUD, and to compare it with both CBT4CBT-Buprenorphine alone and the treatment as usual (TAU). Patients (*n* = 90) who have newly initiated buprenorphine in the past 90 days are planned to be recruited. Comprehensive measures on demographics, various conditions/constructs, and outcomes will be collected from medical charts and survey instruments. Additionally, neurophysiological outcomes and neurocognitive inhibitory controls will be measured using the NEXUS-10-MKII physiological system with BioTrace+ software and computerized Drug Go/NoGo Task, respectively. Qualitative analysis of interviews with *N* = 2 RCs and *N* = 15 participants will also be conducted. The study will be the first to examine the effectiveness of the remotely delivered RC + CBT4CBT-Buprenorphine intervention on drug use (during the first 8 weeks and follow-up) and retention in care, as well as on various neurophysiological and cognitive performances in comparison to CBT4CBT-Buprenorphine alone and TAU.

**Clinical Trial Registration:** This study was registered at ClinicalTrials.gov (NCT06102200, www.clinicaltrials.gov/) on August 31, 2023, with a title, An Integrated Intervention Involving Recovery Coaching and Cognitive Behavioral Therapy for Opioid Use Disorder (OVERCOME 2).

## Introduction

1.

Opioid use disorder (OUD) affects an estimated 2.1 million people in the US and is expected to continue to increase. [1] Medications for opioid use disorder (MOUD), including buprenorphine, have been demonstrated to be effective at producing substantial reductions in opioid use and other illicit drugs, risk of overdose, criminal activity, and other risky drug-related behaviors. [2–6] Despite the effectiveness of MOUD, retention to buprenorphine is suboptimal [7] as a recent systematic review indicated that only 57% of individuals who initiate MOUD are retained 6 months later, and 46% in 12 months. [8] In addition, high rates of polysubstance use among people receiving MOUD were associated with lower adherence and retention to MOUD. [9,10] As such, integrating additional therapeutic strategies into MOUD protocols to address these deficits is urgently needed.

Peer recovery coaching is a form of nonclinical, peer support aimed at helping individuals with substance use disorders (SUDs) achieve and maintain recovery. [11] We have developed a recovery coaching assertive community engagement (ACE) model by adapting from the evidence-based model of assertive community treatment (ACT) for persons living with serious mental illnesses. [12–14] Recovery coaches (RCs) are individuals with lived experience with substance use and successful recovery. In addition to their lived experience, recovery coaches receive formal training on substance use coaching following the assertive community engagement (ACE) model and receive ongoing supervision. There is evidence that this RC recovery coaching improves initiation, long-term engagement in the recovery process and reduces substance use. [15–18] Nonetheless, our recent systematic review revealed that recovery coaches have not been shown to improve OUD outcomes beyond MOUD initiation. [19]

Cognitive behavior therapy (CBT) is an integrative approach involving cognition, affect, and environment and emphasizes learning new skills and coping behaviors in order to achieve abstinence and avoid relapse. [20] Although CBT can be delivered by professionals, including social workers, psychiatrists, and psychologists, using various modes of delivery, such as in-person and via computer-based interfaces, a computer-based training version of CBT for SUDs, known as CBT4CBT, has emerged as a promising tool for delivering CBT. [21–24] Nonetheless, a recent systematic review of randomized clinical trials (RCTs) combining computerized CBT and pharmacotherapy showed that the addition of computerized CBT only produces a small, significant effect in drug use, [25] but no effect was seen in the two buprenorphine trials. [26,27] However, a pilot RCT examined a web-based CBT (CBT4CBT-Buprenorphine) training adapted for office-based buprenorphine, and found that those who were randomized to receive CBT4CBT-Buprenorphine submitted more urine samples that were negative for opioids (91.3% vs 63.9%) and for all drugs tested during the treatment than those assigned to buprenorphine alone (81.6% vs. 29.9%). [28] However, CBT4CBT module completion was suboptimal, as participants completed only about half (52.5%) of the intended 8 CBT4CBT modules).

To complement the effect of CBT4CBT, we developed and tested an integrated intervention that combines Recovery Coaching and CBT4CBT-Buprenorphine (RC + CBT4CBT-Buprenorphine), guided by the well-established behavioral change model of Information, Motivation, Behavioral Skills (IMB) model. [29] The IMB model asserts that information, motivation, and behavioral skills are fundamental determinants that influence individuals’ behavior change. The CBT4CBT component will provide information related to substance use (several modules, which includes understanding drug use, patterns of substance use, triggers) and adherence to buprenorphine (module on buprenorphine, which includes an introduction to buprenorphine, what to expect in treatment, handling common problems, and talking to family members about OUD and buprenorphine, and encouraging patients to adhere to their treatment program and stay on buprenorphine). The Recovery Coach component will enhance motivation. Finally, both components, CBT4CBT and Recovery Coach, will improve behavioral skills in that the CBT4CBT program will teach the skills, whereas the recovery coach will provide role modeling and reinforce skills, encourage the participant to practice skills, and promote completion of modules and homework, thereby leading to a reduction of drug use and improved retention in buprenorphine treatment. Our group found that adding an RC to CBT4CBT-Buprenorphine improved adherence to the CBT modules and improved drug use outcomes compared to treatment as usual (TAU) with buprenorphine alone. [30]

The critical gap, however, is that we did not compare the integrated recovery coach intervention RC + CBT4CBT-Buprenorphine to CBT4CBT-Buprenorphine alone nor assess retention in care. Therefore, the additional benefit of adding a recovery coach to CBT4CBT-Buprenorphine is unknown. An additional research gap is the examination of craving and physiological arousal in response to drug cues, as well as excessive responsiveness to negative events, which may contribute to the low rates of adherence and recovery among individuals receiving MOUD. [31,32] A recent RCT [33] demonstrated that the CBT4CBT intervention showed a trend towards reduction in attentional bias for drug, which suggests that high levels of engagement with CBT4CBT have the potential to improve cognitive control over drug cues and triggers. However, engagement with this intervention is key to such improvements in cognitive control; therefore, integrating recovery coaches into the intervention may represent an effective way to enhance engagement with CBT4CBT. Building on this plausible mechanism, we attempt to assess the effect of RC + CBT4CBT-Buprenorphine on inhibitory control over drug cues using the Drug Go/NoGo Task adapted for opiate cues in individuals with opioid use disorder.

To fill those gaps, the present OVERCOME II (**O**UD Inter**ve**ntion **R**ecovery **C**oach CBT and **O**UD **Me**dications II) randomized clinical trial study proposes to test the efficacy of RC + CBT4CBT-Buprenorphine for reducing nonprescribed substance use and improving buprenorphine retention compared to TAU and CBT4CBT-Buprenorphine alone (Aim 1), to explore neurocognitive and physiological mechanisms of action of the integrated intervention (Aim 2), and to qualitatively evaluate our RC + CBT4CBT-Buprenorphine intervention to be able to refine the treatment intervention (Aim 3).

## Methods

2.

### Setting

2.1.

The study will be conducted at the Prisma Health Recovery Program (PHRP) in Greenville, South Carolina. This office-based buprenorphine program is staffed by one part-time physician, two full-time nurse practitioners, two full-time addiction registered nurses, one full-time substance use counselor, and one part-time social worker. We have access to part-time psychiatrists (1.5 days each week staffed by 3rd psychiatry residents). The OVERVOME II study is built upon a pilot OVERCOME I study that compared outcomes only between TAU and RC + CBT4CBT-Buprenorphine. [30] The OVERVOME II study is funded by the National Institute on Drug Abuse (NIDA) as a project of the National Institutes of Health (NIH) HEAL initiatives, approved by the Prisma Health IRB (1930664), and registered in the ClinicalTrials.gov (NCT06102200).

### Study arms and interventions

2.2.

#### Treatment as usual (buprenorphine only) arm:

TAU consists of weekly, bi-weekly or monthly visits (at the discretion of the provider) in-person or virtually at an outpatient buprenorphine clinic. Beyond the prescription of buprenorphine, psychosocial support will be provided as the standard of care in the clinic. When a patient needs additional support, the provider schedules an appointment with a counselor.

#### CBT4CBT-Buprenorphine alone arm:

Participants will be provided with the 8-session (module) self- directed CBT4CBT-Buprenorphine system for teaching with one module on the basics of buprenorphine and 7 CBT core skills tailored around issues related to buprenorphine and OUD and other SUDs: (1) introduction to functional analysis of substance use; (2) strategies for recognizing and coping with craving; (3) refusal skills and assertiveness; (4) training in problem solving skills; (5) strategies for recognizing and changing thoughts; (6) decision making skills; (7) how to use CBT skills to reduce HIV/HCV risk. Each module takes 30 min to complete and includes on-screen narration, animation, quizzes, and interactive exercises to teach and model effective use of skills. Modules end with a practice exercise. Study coordinators will instruct participants about the proper use of the CBT4CBT-Buprenorphine system at baseline.

#### Recovery Coach + CBT4CBT-Buprenorphine arm:

This intervention follows the ACE model with approaches to provide a holistic, person-centered, and strength-based support in four big areas: emotional/motivational, informational, instrumental, and affiliational areas. [34] (Table 1) Core characteristics of the ACE model include the team approach (RC integrated with the buprenorphine recovery program team, including addiction medicine clinicians, registered nurses, social workers, and substance use counselors). Recovery coaching services are provided where patients live and work: personalized care; continuous care with trusted team members; flexible care; comprehensive care; and services when they are needed. FAVOR-Greenville has developed and continually maintains a 20-page community directory of resources. RCs are trained as both Certified Peer Support Specialists and Certified Assertive Community Engagement Specialists under the National Association of Alcohol and Drug Abuse Counselors. In addition to formal training, they are required to have 1 year or more in recovery and adhere to the FAVOR code of conduct. Two hired Prisma Health recovery coaches were trained in the use of CBT4CBT-Buprenorphine by an expert in CBT and received ongoing supervision to ensure adherence to the study protocol.

The first encounter with the recovery coach will occur at the baseline (RC + CBT4CBT-Buprenorphine arm only) after participants are deemed eligible and have completed all research assessments. During this first encounter, the recovery coach will perform a needs assessment using recovery capital matrix, based on which the recovery capital matrix, dyad of RC and participant will discuss a customized recovery plan for 12 weeks, always starting with the capital domain that requires more immediate attention in addition to explaining the 8-week CBT4BT-Buprenorphine program and instructing the participants to start completing the modules. RCs and participants will meet once a week, virtually or in person, where they will discuss the CBT4CBT-Buprenorphine module completed, resolve questions and doubts, complete practice exercises, and help with the homework. Recovery coaching services will be delivered via Zoom calls, phone calls, and text messages, and required to initiate at least one meaningful contact (video Zoom) and 3 check-ins (i.e., text message, email, and/or quick call) per week. In addition, the RCs will assess the status of participants’ recovery capital and move towards the next capital needing attention, and will have access to funds capped at $500 per participant to be used at their discretion for providing personalized support services to participants during the 8-week treatment period. The RC will assume responsibility for the ongoing therapeutic relationship. All RCs will be supervised by a senior recovery coach on a weekly basis throughout the course of the treatment.

### Participants defined by inclusion and exclusion criteria

2.3.

This study plans to recruit a total of *N* = 90 participants with OUD receiving buprenorphine. Inclusion criteria for participating in this study include: (1) adults 18 years or older; (2) DSM-V diagnosis of OUD; (3) currently receiving sublingual buprenorphine/naloxone and/or buprenorphine; (4) have initiated buprenorphine within last 90 days from baseline; (5) willing to accept a random assignment to either standard of care, CBT4CBT-Buprenorphine or RC + CBT4CBT-Buprenorphine; and (6) having adequate computer skills (verified using computer literacy survey). Exclusion criteria: (1) having a severe medical or psychiatric disability that could impair ability to perform study-related activities (determined by the clinician); (2) being unable to independently read and/or comprehend the consent form or other study materials; (3) being unable to read/speak English; and (4) having current suicidal ideation based on the Patient Health Questionnaire-9.

### Recruitment process

2.4.

Participants will be recruited (brochures, active referrals from clinicians, research coordinators approaching patients in the clinic, and participant referrals) Potential eligible patients will first be identified through medical chart reviews. Eligible participants who express interest in learning about our study will have a discussion with a research coordinator. Prior to the administration of any study measures, the research coordinator will obtain verbal consent for screening, which briefly describes the study and reinforces the confidentiality of all survey information. Interested patients who are eligible for the study after the initial screen will sign a written informed consent document.

### Assessment schedules and incentives

2.5.

Research assessments will be completed at baseline (randomization), during weekly visits 1–8 of treatment, and then at follow-up assessments 1, 3, and 6 months after the completion of the treatment period. Major research visits (baseline, end of treatment, and follow-ups) will be conducted in person, while all other weekly research visits (i.e., 1–7) will be conducted virtually or in person, based on participant preference. During visits, participants will complete various research materials, including questionnaires, clinical interviews, and saliva drug tests. Participants will self-administer the saliva drug tests while observed virtually by the research coordinator. Participants will be compensated $40 for the baseline session, $20 for visits weeks 1–7, and $40 for week 8 (i.e., end of treatment) and three follow-ups. Participants will receive $50 for the first neuro laboratory session and $75 for the second one. Finally, participants involved in Aim 3 (*N* = 15) will be compensated $25 for participating in the interview. The maximum amount of compensation will be $465/$490.

### Randomization, concealment, blinding and data management

2.6.

The participants will be randomized in a 1:1:1 ratio with varying masked block sizes to equally distribute *N* = 30 participants to each arm… The random allocation will be concealed, passcode-protected and stored in a secure Research Electronic Data Capture (REDCap) database. Only designated study coordinators will have access to the random allocation code and will dispense upon the availability of patients eligible for enrollment and randomization. Due to the open-label nature of the interventions, it is not feasible to blind the participants or the research coordinators duing assessments conducted at the research visits. However, we will use standardized treatment manuals and protocols to ensure the consistent delivery of the intervention and study assessments across participants, thereby maintaining internal validity of our study and minimizing the risk of potential bias due to the unblinding.

The REDCap database will also be used to collect and manage data, ensuring that all data will be entered into REDCap with no personal identifiers, and source documents will identify participants by study ID. Access to computers used for data entry, management, and analysis will be passwordprotected and limited to the study coordinators. Personal identifying information (including locator information) will be kept in a secure area and a locked file cabinet. More details will be described and specified in a separate data management plan (DMP) document following the HEAL-initiative data ecosystem guidelines. A tentative schematic CONSORT diagram depicting the entire study flow from enrollment steps to the analysis phase is presented in Fig. 1.

### Measures

2.7.

All study measures for primary, secondary, and exploratory outcomes will be assessed using survey instruments and medical charts listed in Table 2 along with purposes and assessment time frames. Baseline demographic characteristics will include age, gender, ethnicity, race, sexual orientation, education, marital status, annual income, housing status, employment status, handedness (right- or left-handed), and method of transportation. Baseline disease characteristics will include hepatitis C infection, HIV infection, and comorbidities that include diabetes, liver disease, renal disease, and chronic pulmonary diseases. Retention in care will be assessed based on medical chart data on buprenorphine prescription records. All measures in Table 2, except for those specific to RC or CBT4CBT activities, will be assessed for all participants. The primary outcome for aim 1 will be longitudinal weekly positive responses for any drug use ascertained by saliva toxicology test during the 8-week study period. To this end, the study will use a 14-panel saliva drug test (Lochness Medical Supplies, Inc.) that screens for alcohol, amphetamine, barbiturate, buprenorphine, benzodiazepine, cocaine, fentanyl, MDMA, methadone, methamphetamine, opiate, oxycodone, THC/Cannabinoids, and phencyclidine (PCP). A secondary outcome will be retention in care, to MOUD in particular, where MOUD includes buprenorphine, methadone, or extended-release naltrexone.

### Aim-by-aim statistical analytic plans

2.8.

A detailed statistical analysis plan (SAP) will be documented in a separate file, and thus, here we briefly describe analysis plans. All analyses will be performed using SAS v9.4. (SAS inc, Cary, NC, USA) and R software.

#### Aim 1 analysis plan:

The primary analytic sample will include all randomized participants, referred to as the intention-to-treat (ITT) sample. For the analysis of data from this ITT sample, the group membership will remain unchanged as randomized, even if participants cross over to the other groups during the trial. We will also conduct modified ITT (mITT) analysis, including only participants in the intervention arms who opened at least one CBT4CBT module, and per-protocol (PP) analysis, including those who completed 50% or more modules and/or those who engaged with a RC at least once. To compare the longitudinal primary binary outcome of drug-free test results across the three groups, we will apply generalized mixed-effects linear models to the ITT sample. The primary comparisons will be conducted in pairwise comparisons with a Bonferroni-corrected two-tailed significance level of 0.017 = 0.05/3: 1) RC + CBT4CBT-Buprenorphine vs. CBT4CBT-Buprenorphine; 2) RC + CBT4CBT-Buprenorphine vs. standard of care; and 3) CBT4CBT-Buprenorphine vs. standard of care. As this is an RCT with ITT sample, no adjusting variables will be included in the model. The analysis of secondary outcomes, such as retention in care during the study and follow-up periods, will be similarly conducted.

#### Aim 2 analysis plan:

First, to test whether changes from baseline to the end of treatment in scores of neurophysiological responses (SCL, respiration, and HRV), Drug Go/NoGo Task commission errors, coping strategies, self-reported craving, and are different between RC + CBT4CBT-Buprenorphine and other groups in a pairwise comparison manner, we will use *t*-test or Wilcoxon rank sum test (depending on the results of normality test). If adjustment for covariates is deemed necessary, we will apply analysis of covariance (ANCOVA). Second, to test whether outcome scores themselves are different, overall or by group, between baseline and the end of the first 8 weeks, we will use a paired t-test or Wilcoxon signed-rank sum test. Lastly, correlation analysis will be used to explore the association among physiological responses, treatment engagement indicators (i.e., number of modules completed, number of CBT4CBT homework assignments completed, and number of contacts with the recovery coach) and Drug Go/NoGo Task (commission errors), coping strategies, self-reported craving, and ERP components (N200, P300, ERN).

#### Aim 3 analysis plan:

Interviewers’ transcriptions will be uploaded into NVIVO, a qualitative data analysis program that facilitates the rapid organization and retrieval of thematic data. The qualitative analysis team will develop a preliminary coding scheme. Preliminary codes will include barriers and facilitators of implementation; perceptions of strengths, weaknesses, rewards, and burdens; and recommendations to improve the intervention. The initial coding scheme will be applied to a subset of data, and will be subsequently revised and reapplied to the data in an iterative fashion until it is deemed sufficiently parsimonious and comprehensive.

### Handling missing data

2.9.

Every effort will be made to limit the amount of missing primary outcome data in this study. Although the primary analytic strategy involves analyzing available data using mixed-effects models, which is unbiased under missing at random (MAR) assumptions, we will conservatively assume in a sensitivity analysis that missing saliva samples will be considered drug-positive based on the current literature, [23,26,28] that is, the worst-case scenario imputation. In addition, we will also apply last-observation-carried-forward (LOCF) imputation as well as fully specific conditional specification multiple imputation methods, [40] which are applicable to non-ignorable missing data. Characteristics of patients who are lost to follow-up will be compared to those who complete the study to assess the degree of any selection bias due to attrition.

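### Section 2.9 presents standard FCS multiple imputation as covering non-ignorable missing tests, which it does not, and calls missing = positive conservative although its direction for a between-arm difference depends on missingness by arm

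*Protocol article*

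**What the plan says.** Section 2.9 (Handling missing data) describes the primary strategy as "analyzing available data using mixed-effects models, which is unbiased under missing at random (MAR) assumptions". Three sensitivity analyses follow:

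- Missing = positive: "we will conservatively assume in a sensitivity analysis that missing saliva samples will be considered drug-positive based on the current literature", glossed as "that is, the worst-case scenario imputation".
- LOCF: "we will also apply last-observation-carried-forward (LOCF) imputation".
- Multiple imputation: "fully specific conditional specification multiple imputation methods, [40] which are applicable to non-ignorable missing data". I read this as fully conditional specification.

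The section also plans to compare the characteristics of participants lost to follow-up with those of completers. It mentions no delta shift, pattern-mixture model, selection model or tipping point.

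The Aim 1 analysis plan (section 2.8) tests three pairwise differences, each at a "Bonferroni-corrected two-tailed significance level of 0.017 = 0.05/3". Under section 2.2, only the RC arm has coaches, who are "required to initiate at least one meaningful contact (video Zoom) and 3 check-ins (i.e., text message, email, and/or quick call) per week".

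**The concern.** In opioid use disorder a missed drug test may well be related to drug use, so MAR is the assumption that most needs probing. Two statements in section 2.9 affect how that probing will be read.

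First, FCS draws each missing value from conditional models fitted to observed data. It departs from MAR only if a departure is deliberately built in, and none is stated. As written, two MAR analyses could agree and be reported as evidence of robustness to non-ignorable missingness.

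Second, coding every missing test as positive gives the highest possible positive rate in each arm. The trial, however, tests differences between arms. The rule misclassifies exactly those missing tests that were truly negative. If the comparator has more of them than the RC arm, the rule moves the difference towards RC. A rule that can do this should not be labelled conservative in advance.

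**Working it through.** **The plan's own figure.** Section 2.10 claims more than 80% power for 38% vs 58% with 27 per arm, 8 tests, ICC below 0.1 and two-sided alpha 0.017. Effective n per arm = 27 × 8 / (1 + 7 × ICC).

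- ICC 0.10: 216/1.70 = 127.1, power 79.4%.
- ICC 0.05: 216/1.35 = 160.0, power 88.8%.

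The claim reproduces to within a point at the boundary and is not in dispute. Only the 20-point planning difference, the alpha and the ICC are used below. All missingness rates below are assumptions, because the article gives none by arm.

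**Step 1: what standard FCS does when missingness depends on the unseen result.** If a share a of positive tests and b of negative tests are missing, the observed positive rate is p(1 − a) / [p(1 − a) + (1 − p)(1 − b)]. With p = 0.58:

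- a = 0.30, b = 0.10: 0.406 / (0.406 + 0.378) = 0.518.
- a = 0.50, b = 0.10: 0.290 / (0.290 + 0.378) = 0.434.

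A simulation of one arm (4,000 participants, to show bias rather than noise; 8 correlated weekly tests; chained logistic imputation from the other weeks; one run per row) gave:

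| ICC | Missing, positive / negative tests | Truth | Observed | FCS |
|---|---|---|---|---|
| 0.1 | 20% / 20% | 0.573 | 0.573 | 0.572 |
| 0.1 | 30% / 10% | 0.580 | 0.518 | 0.521 |
| 0.1 | 50% / 10% | 0.575 | 0.432 | 0.438 |
| 0.5 | 30% / 10% | 0.571 | 0.509 | 0.535 |
| 0.5 | 50% / 10% | 0.580 | 0.433 | 0.493 |

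FCS is right when missingness is unrelated to the result. Otherwise it stays near the observed rate at the plan's ICC. At ICC 0.5 the other weeks recover about two-fifths of the gap, for example (0.535 − 0.509) / (0.571 − 0.509) = 0.42.

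**Step 2: missing = positive, with missingness unrelated to the result.** An arm's rate becomes p + (1 − p)m, where m is the share missing. The difference (comparator minus RC) moves by (1 − p_C)m_C − (1 − p_RC)m_RC.

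*No true difference, 50% positive in both arms.* RC at 10% missing: 0.50 + 0.50 × 0.10 = 0.55. Comparator at 20% and 30%: 0.60 and 0.65. The artefact is 5-10 points, a quarter to a half of the 20-point planning difference.

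*No true difference, 58% positive in both arms, RC 10% missing (62.2%).* Comparator at 20%, 30% and 40% missing: 66.4%, 70.6% and 74.8%. The artefacts are 4.2, 8.4 and 12.6 points. With effective n = 30 × 8 / 1.7 = 141.2 per arm, the chance of a significant result favouring RC is 4.9%, 18.5% and 45.7%, against a nominal 0.017/2 = 0.85%.

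*True 58% (TAU) vs 38% (RC), a 20-point difference:*

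| Missing TAU / RC | TAU | RC | Difference |
|---|---|---|---|
| 10% / 10% | 62.2% | 44.2% | 18.0 points |
| 10% / 30% | 62.2% | 56.6% | 5.6 points |
| 30% / 10% | 70.6% | 44.2% | 26.4 points |

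Break-even is 0.42 × m_TAU = 0.62 × m_RC, or m_TAU = 1.48 × m_RC. With 10% missing in RC, the rule inflates this difference only once TAU passes 14.8%.

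**Step 3: missing tests more often positive.** Let the *observed* rate be 50% in both arms and let 80% of missing tests be positive. The true rate is 0.50 + 0.30m: 53% in RC (10% missing) and 56-59% in the comparator (20-30% missing). The true difference is 3-6 points, MAR gives 0, and missing = positive gives 5-10.

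**The case against.** The strongest reply is that the plan does look beyond MAR. Missing = positive is an explicit MNAR scenario at the extreme, and LOCF is also not a MAR method. A reader might infer from the FCS error that MAR goes untested, but section 2.9 does not support that. In step 3 the primary analysis and missing = positive bracket the truth, which is what a sensitivity pair is for, and there the MAR analysis errs against RC.

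A reader might also infer that missing = positive will favour RC in this trial. The documents do not show that either. The only planning figure is 10% attrition, applied equally to all arms (section 2.10), and under equal missingness the rule shrinks the difference. Coaching contacts are separate from the research visits at which saliva is collected, and payment and the choice of visit format do not differ by arm (section 2.5). The coached arm has extra tasks, so it could miss more tests. Unequal missingness is plausible in either direction.

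Finally, section 2.8 announces a separate SAP, and the cited imputation source is not available here. An MNAR form of FCS may be intended, and the absence of delta values from an article is no fault in itself.

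All of this stands, and it limits the point. It does not rescue the sentence about FCS, which attributes to the method a property that its standard form lacks, nor an unconditional label for a rule whose direction is conditional.

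**Conclusion.** The statement on FCS is wrong as written: without a stated departure it is a second MAR analysis. Under the assumed mechanisms and the plan's ICC, it missed one arm's true rate by 5.9 points (58.0% vs 52.1%) or 13.7 points (57.5% vs 43.8%). The effect on a between-arm difference would depend on how the mechanisms differ by arm.

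Missing = positive is one legitimate extreme scenario. If missingness is unrelated to the result and RC does no worse than its comparator, the rule is conservative for the contrast when missingness is equal or higher in the RC arm. It favours RC when the comparator misses clearly more tests (a 5-10 point artefact at 50% positivity with 10% vs 20-30% missing). What section 2.9 lacks is a graded, arm-specific departure from MAR, not any departure at all.

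Only the robustness claims are affected. The primary model and sample size are unchanged. The change is worth making before the data are analysed.

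**What to change.** - Describe standard FCS as a MAR analysis. Include EMR/PDMP prescription status (Table 2) as an auxiliary variable, since it does not depend on attending a visit. The 7-day TLFB is scheduled at the same visits as the saliva test, so it will often be missing with it and adds little.
- Add delta-adjusted FCS: shift the log-odds of a positive result in missing weeks by arm-specific amounts, from 0 up to the limit where every missing test is positive. Report the tipping point for each pairwise comparison. Include the case with missing = positive in RC and MAR in the comparator.
- Drop *conservatively* and *worst-case* as descriptions of the between-arm contrast, and report missingness by arm beside the missing = positive result.
- Replacing LOCF is optional.

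The cost is revised wording here and in the SAP, a few extra imputation runs, and possibly a less favourable robustness statement. No new data are needed.
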